#### 2.6.6. Water Supplementation

At 9:00 AM, subjects in the WS group will drink 400 mL purified water within 5 min with uniform cups in one designated place, while those in NW group will not drink any water or beverages in another designated place. Subjects in NW group will not be told the intervention of WS group. During the interval before the next test, all subjects will be asked to sit at their own seat without physical activity. They will be asked not to eat foods, drink water/beverages, and urinate. One hour after water supplementation (at 10:05 AM), blood pressure and blood glucose will be measured again in designated place (test 2: after water supplementation). Urine samples will be collected, stored and tested again (test 2). At 10:25 AM, cognitive performances, mood and subjective sensation of satiety, hunger, sleepiness and thirst will be measured again (test 2). Temperature and humidity will be recorded at 8:00 AM. During the period of the study, subjects can quit at any time for side effects, such as syncope. The study procedure is shown in Figure 2.

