## 2. Methods and Analysis

### 2.1. Study Hypothesis

One hypothesis is that hypohydration state will impair cognitive performances and mood. Another hypothesis is that water supplementation will improve hydration state, cognitive performances and mood.

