#### 2.6.4. Assessment of Baseline Indicators

On day 8 (the day before the supplementation day), all subjects will be asked to be fast without any foods and fluid from 8:00 p.m. They will be asked to sleep before 11 PM in the evening and not urinate after sleep until getting up in the next morning to collect first urine samples. In addition, they will be asked not to do high intensity exercise before the test. Anyone who fails to meet the above requirements needs to let investigators know. The first morning urine samples in the water supplementation day will be collected in sterile disposable urine sample cup by themselves and will be tested immediately by professional lab technicians in hospital (test 1).

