#### 2.6.5. Groups of Subjects

On day 9 (the water supplementation day), all subjects will be asked to arrive at the designated place at 8:00 AM. After being encoded according to student ID, subjects will be randomly assigned to the water-supplementation group (WS group, 34) and no water-supplementation group (NW group, 34) using random number table to generate random sequence. Baseline height, weight, waist circumferences, blood pressure and blood glucose will be measured (test 1: before water supplementation) following the standardized procedures. The first morning urine samples will also be collected and tested. At 8:30 AM, cognitive performances, mood and subjective sensation of satiety, hunger, sleepiness and thirst will be tested (test 1).

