**Figure 2 ijerph-14-00966-f002:**
[figure not shown]
The study procedure. Note: H (Height); W (Weight); WC (Waist circumference); BP (Blood pressure); BG (Blood glucose); CP (Cognitive performances); POMS (Profile of Mood States); VAS (Visual Analogue Scales).

**Table 1 ijerph-14-00966-t001:** All items from the World Health Organization Trial Registration Data Set (SPIRIT checklist, item 2b).

Data Category	Information
Registration number	ChiCTR-IOR-15007020, Chinese clinical trial registry
Registration State	1008001 Prospective registration
Public title	The effect of hydration on cognitive performance
Scientific title	The effect of hydration on cognitive performance
Approval of ethic committee	Chinese Nutrition Society biomedical ethics committee
Ethical approval project identification code	CNS2015001
Date of approved by ethic committee	1 December 2015
Study type	Interventional study
Study design	Randomized parallel controlled trial
Key inclusion and exclusion criteria	Inclusion criteria: Aged between 18~25; Male; In health state, without metabolic disease, oral diseases, and so on. Exclusion criteria: Aged < 18, or age > 25; Female; With metabolic disease, oral diseases, and other diseases.
Interventions	Water supplementation
Outcomes	Urine osmotic pressure, Blood pressure, Mood, Thirsty, Cognitive performance
Collecting samples	Urine
Recruitment state	Finished
Randomization Procedure (please state who generates the random number sequence and by what method)	Primary sponsor generates random sequence with random number table.

**Table 2 ijerph-14-00966-t002:** The schedule of enrolment, interventions, and assessments.

	Enrolment	Allocation	Post-Allocation	Close-out
Timepoint	1 February 2016	14 March 2016	14 March 2016	30 March 2016
Enrolment:				
Eligibility screen	X			
Informed consent	X			
Allocation		X		
Interventions:				
Water supplementation			X	
Assessments:				
Baseline anthropometric measurements variables: blood pressure, height, weight, waist circumference	X		X	
Outcome variables: cognitive performances, mood, subjective sensation			X	X

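### No void is scheduled between the first morning urine and the 9:00 AM drink, so the test 2 urine can mix pre-drink with post-drink urine and understate the effect on hydration

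*Protocol article*

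**What the plan says.** All references are to the protocol article.

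- **Overnight and first void.** Section 2.6.4 asks subjects to "not urinate after sleep until getting up in the next morning to collect first urine samples". Section 2.6.5 says "all subjects will be asked to arrive at the designated place at 8:00 AM" and then, among the on-site procedures, "The first morning urine samples will also be collected and tested". The first void may therefore be at home on rising, or on site before the 8:30 AM tests.
- **Between that void and the drink.** "At 8:30 AM, cognitive performances, mood and subjective sensation of satiety, hunger, sleepiness and thirst will be tested (test 1"). No void is listed here.
- **Drink.** "At 9:00 AM, subjects in the WS group will drink 400 mL purified water within 5 min" (2.6.6).
- **After the drink.** For both groups: "They will be asked not to eat foods, drink water/beverages, and urinate". Blood pressure and glucose follow at 10:05 AM. Urine collection is listed next, before the 10:25 AM tests.
- **Number of samples.** Section 2.10 has urine collected twice on day 9, which leaves no third, pre-drink collection.
- **Use of the result.** Section 2.1 hypothesises that "water supplementation will improve hydration state, cognitive performances and mood". Table 1 lists the outcomes as "Urine osmotic pressure, Blood pressure, Mood, Thirsty, Cognitive performance". Section 2.11 defines hypohydration as urine osmolality above 800 mOsm/kg, and section 2.19 analyses the change in urine indices with the repeated-measures model.

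**The concern.** A urine sample averages everything the kidney has produced since the bladder was last emptied. For test 2 that period starts at the first morning void, not at 9:00 AM. In the water group, concentrated urine made before the drink is pooled with the dilute urine made after it. In the no-water group both portions are about equally concentrated, so pooling changes little. The same rule in both arms therefore does not cancel: it shrinks the contrast.

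The indices at stake are osmolality, specific gravity, the electrolyte concentrations and hypohydration status. The time since the last void is not fixed, so it also adds between-subject noise. A reader of the results could take the water to have changed hydration less than it did.

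**Working it through.** The plan states no figure on this point, so there is nothing to reproduce. The check is a mass balance.

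**Inputs from the article:** drink at 9:00 AM; test 2 from 10:05 AM, so 65 min of post-drink urine; on-site first void between 8:00 and 8:30 AM, so a gap T of 30 to 60 min before the drink. A void on rising gives a longer gap of unknown length.

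**Assumptions, not in the article:** T up to 150 min (a void at 6:30 AM); flow before the drink 0.75 mL/min; mean water-group flow F after it of 1 to 4 mL/min; pre-drink osmolality 900 mOsm/kg; constant solute excretion; no-water urine unchanged across 9:00 AM; no unscheduled void before 9:00 AM.

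**Formula.** Pre-drink volume Vpre = 0.75 × T. Post-drink volume Vpost = F × 65. By volume weighting,

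share of true fall measured = Vpost / (Vpre + Vpost) = 65F / (0.75T + 65F).

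The share depends only on the two volumes. The 900 mOsm/kg and the constant solute load matter only for the examples in mOsm/kg.

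| Gap T | Vpre | F = 1 (65 mL) | F = 1.5 (97.5 mL) | F = 3 (195 mL) | F = 4 (260 mL) |
|---|---|---|---|---|---|
| 30 min | 22.5 mL | 74% | 81% | 90% | 92% |
| 60 min | 45 mL | 59% | 68% | 81% | 85% |
| 150 min | 112.5 mL | 37% | 46% | 63% | 70% |

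**Example at F = 1.5.** Post-drink osmolality = 900 × 0.75 / 1.5 = 450, a true fall of 450. The measured fall is 450 × 0.8125 = 366 (T = 30), 450 × 0.684 = 308 (T = 60) or 450 × 0.464 = 209 (T = 150).

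**Extreme corner, F = 1 and T = 150.** Post-drink osmolality = 675, a true fall of 225. The measured fall is 225 × 65/177.5 = 82, so the sample reads 818. That is above the 800 cut-off although the urine formed after the drink is below it.

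**Sensitivity to collection time.** If urine were collected as late as 10:25 AM, 85 min would replace 65. The F = 1, T = 60 cell would rise from 59% to 85/(45 + 85) = 65%.

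**With a void at 9:00 AM.** T = 0, Vpre = 0, and the share is 100% for any F.

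**Can it be corrected afterwards?** Not well from what is described. No void time is said to be recorded, and section 2.10 measures urine volume to the nearest 0.1 kg, about 100 mL. That is of the same order as, or larger than, the 22.5 to 112.5 mL carried over.

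**The case against.** Several points on the other side stand.

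- **The gap may be short.** Section 2.6.5 supports an on-site first void, which gives 30 to 60 min. At 30 min only 8% to 26% of the fall is lost. The 37% figure needs both a long gap and a flow that rises by only a third after 400 mL.
- **A void before 9:00 AM is not barred.** The ban covers only the interval after the drink, and two collections do not exclude an uncollected void. Some subjects may carry over little or nothing. The procedure figure is not shown.
- **Hydration is a supporting outcome.** The objectives in the Introduction rank cognition first and mood second, and the sample size rests on digit span. A reader might infer from Table 1 that urine osmolality is the leading registered outcome because it comes first, but that list is unranked.
- **A null result is unlikely in the middle of the range.** With an assumed SD of 250 mOsm/kg and 31 per arm (34 × 0.9 = 30.6), the standard error is 250 × √(2/31) = 63.5. Power is then about 90% for a fall of 209 and above 99% for 308.
- **The fix is not perfect.** Urine made just after 9:00 AM, before the water takes effect, stays in the sample.

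A reader might also infer that comparing first morning urine with later urine biases the trial in itself. That shift is common to both arms, and the randomised comparison handles it. Nor does overnight urine enter test 2, because the first morning void has already emptied it.

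None of this removes the core point: the schedule neither requires nor times a void before the drink, and any pre-drink urine left in the bladder shrinks the contrast.

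**Conclusion.** The point holds as a sampling weakness in the hydration outcome. The direction, toward no difference, follows from mass balance as long as no-water urine stays about as concentrated as before. The size cannot be fixed from the article. On the assumed flows, the measured share of the true fall is 74% to 92% at a 30 min gap, 59% to 85% at 60 min and 37% to 70% at 150 min, and it is higher for anyone who voids unprompted before 9:00 AM.

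It would be wrong to conclude that most of the hydration effect is lost, or that the trial's main comparison is compromised. The first needs the long-gap, low-flow corner, which the article does not establish. The second fails because cognition and mood are not measured through urine. The bias is conservative and cannot produce a false hydration benefit. The point still deserves action, because improved hydration is a stated hypothesis, its change is analysed, and the remedy is nearly free.

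**What to change.** In 2.6.6, add that every subject in both arms empties his bladder just before 9:00 AM and that the time is recorded. Discard that urine, or keep it as a pre-drink sample comparable with test 2. Retain the first morning urine as the measure of overnight hydration, and say in 2.6.4 and 2.6.5 whether it is collected at home or on site.

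The cost is one sentence and one extra void per subject; an assay of that sample is optional. The downside is a smaller test 2 volume in some no-water subjects.

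Table 1 gives recruitment as finished and Table 2 dates the study to February and March 2016. If testing is already complete, state as a limitation that the change in osmolality and the other urine concentrations is likely understated in the water group, by an amount that depends on unrecorded void times.

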### 2.7. Blinding of Data Analysis

Data analysts will analyze the data without being informed which group is water supplementation group or no water supplementation group. The names of groups will be coded as A and B. After data analysis and the finish of summary report, data analysts will be informed the group code.

The schedule of enrolment, interventions, and assessments is shown in Table 2.

### 2.8. Assessment of Fluid Intake

Daily total drinking fluid of the subjects will be collected using a 7-day 24-h fluid intake record by themselves after standardized training to use the fluid intake record correctly. The amount of drinking fluid for each time will be measured by a cup with the nearest of 10 mL. Subjects will pour fluid into the cups to measure the amount when they drink liquid. The method of 7-day 24-h fluid intake record has been used in previous studies and was proved to be reliable. All sources of drinking fluid will be included in, such as boiled water, bottle water, brewed tea, tea drinks, carbonated soft drinks, fruit and vegetable drinks, protein drinks, functional drinks, solid drinks and so on. The type, place, time, and amount of fluid will also be recorded by subjects. To ensure the completeness of 7-day 24-h fluid intake record, questionnaire will be reviewed by investigators every day.

Fluid intake from foods will be assessed with duplicate portion method. All foods consumed by the subjects will be weighted for three consecutive days (including two weekdays and one weekend day). Samples of all foods will be collected and measured according to the national standard of GB 5009.3-2010 by professionals in Analysis Laboratory of Beijing Nutrition Resources Institute. (Daily total fluid intake (mL) = Daily total drinking fluid (mL) + Daily fluid intake from foods (mL)).

### 2.9. Anthropometric Measurements

Height (H) will be measured twice to the nearest 0.1 cm and weight (W) will be measured twice to the nearest 0.1 kg while wearing light clothing and no footwear by trained investigators following standardized procedures with height-weight meter (HDM-300; Huaju, Yiwu, Zhejiang, China) in a standardized time (during 8:00 AM to 8:30 AM in the water supplementation day). 

Waist circumference (WC) will be measured twice at the midpoint between the bottom of the rib cage and the top of the iliac crest at the end of exhalation with the subject standing without clothing covering the waist area to the nearest 0.1 cm by trained investigators with a MyoTape waistline measurer in a standardized time (during 8:00 AM to 8:30 AM in the water supplementation day). (BMI: weight (kg)/height squared (m)]; body surface area (m^2^): (weight (kg)^0.425^ × height (cm)^0.725^) × 0.007184 [24]). 

Blood pressure (BP) will be measured twice to the nearest 2 mmHg by a nurse with electronic sphygmomanometer (HEM-7051; Omrom, Dalian, Liaoning, China) at a standardized time (during 8:00 AM to 8:30 AM in the water supplementation day). Two measurements will be taken after 2-min intervals.

Blood glucose (BG) will be determined once with fingertip blood of the index finger by a professional nurse with a glucometer (One Touch UltraEasy; Johnson, Shenzhen, China) at a standardized time (between 8:00 AM to 8:30 AM on the water supplementation day).

### 2.10. Assessment of Urine Biomarkers

Urine samples will be collected twice in disposable flexible packaging plastic bags by the subjects in the day 9 (the water supplementation day). Urine samples will be stored at +4 °C before assessment. Urine volume will be measured to the nearest 0.1 kg with a desktop electronic scale (YP20001; SPC; Shanghai, China). Urine osmolality will be tested using an osmotic pressure molar concentration meter (SMC 30C; Tianhe, Tianjin, China) with the freezing-point method. Urine-specific gravity (USG) will be tested using an automatic urinary sediment analyzer (FUS-200; Dirui, Changchun, China) with the uric dry-chemistry method. Urine pH will be measured using a urine analyzer (Uritest-180, Uritest; Guilin, China) with the reflective photoelectric colorimetry method. The urine concentrations of potassium (K), sodium (Na) and chloride (Cl) will be tested using an automatic biochemical analyzer (Cobas C501; Roche, Basel, Switzerland) with the ion-selective electrode potentiometer method.

### 2.11. Definition of Hypohydration

The balance between water outputs and water inputs defines hydration state [25]. Hypohydration occurs when water inputs is insufficient to replace free water outputs, which is defined as the urine osmolality is greater than 800 mOsm/kg [26]. 

### 2.12. Visual Analogue Scales (VAS) for Subjective Sensation

VAS is a self-rated 10-cm-line designed to quantitatively measure subjective sensation of satiety, hunger [27], sleepiness [28] and thirst [29]. On the line of VAS, the labels “not at all” and “extremely” will be anchored at the beginning and end. Subjects will be instructed to place a vertical line on it corresponding to their current degree of feeling. The range of scores varies between 0 and 10 according to the length of the line. The higher score means the higher level of corresponding subjective sensation.

### 2.13. Profile of Mood States (POMS)

The self-rating mood questionnaire consisted of seven subscales, 40 adjectives that measured tension, depression, fatigue, vigor, confusion, anger, esteem-related affect and total mood disturbance [TMD: (tension + depression + anger + fatigue + confusion) − (vigor + esteem-related affect) + 100]. TMD is a global estimate of affective state [30]. Method of evaluating score: choose one scale for each adjective which conforms to own situation from five scales (0 not at all, 1 a little, 2 moderately, 3 quite a bit, 4 extremely). All answers will be analyzed through a 5-point rating.

### 2.14. Cognitive performances (CP)

*Digit span forward and backward*: This will be used to assess short-term memory. A list of random numbers will be read out loudly at the rate of one per second by trained investigators. After reading a digit sequence, subjects will be asked to recall the digits in forward or backward order. The digits sequence will begin with three numbers, which should be without recognizable digit patterns on two consecutive trials of the same length. Two incorrect repetitions result in termination of the test. Digit span forward, for example, if the investigator reads ‘‘1 2 3’’, the participant will repeat ‘‘1 2 3’’. Digit span backward, for example, if the investigator reads ‘‘1 2 3’’, the participant will repeat ‘‘3 2 1’’.The number of digit without error will be counted as score respectively for digit span forward and backward [18]. Total score will be used to assess overall performances (Total score = forward score + backward score).

*Digit symbol substitution test*: This test will be used to assess digital decoding ability, visual memory, visual attention, and operating speed. It consists of nine digit-symbol pairs followed by a list of digits (total 90) (for example, 1/_, 2/⊥ ... 7/Λ, 8/X, 9/=). Subjects will be asked to write down the corresponding symbol under each digit as fast as possible within the allowed time (90 s). The number of correct symbols will be measured for score [31].

*Dose-work test*: It will be used to assess the ability of sustained attention. An Aventura Karimov table [32] will be used to evaluate the quality and quantity of dose-work. Subjects will be asked to cross the letter B behind the letter H line by line in 2 min—in an A4 format page filled with eight different letters (A, B, C, E, H, K, N, X) in a random order; total 1200 characters are on one page; each letter appear 150 times. (Reading speed (n/min) = number of already-read letters (n)/2 (min); error rate (%) = number of errors (n)/number of already-read letters (n) × 100%; mental work ability index (IMC) = number of already-read letters (n)/2 (min) × (number of letters had to be crossed − number of errors)/number of letters had to be crossed). 

*Creativity*: Given four kinds of description, such as “usually red”, “usually round”, “usually very noisy”, “usually have wheels”, subjects will be asked to write down the objects as much as possible in accordance with the corresponding description without same type in 5 min [33]. (C-score = log2 (1/P_1_) + log2 (1/P_2_) +…+ log2 (1/P_n_), P= the probability that the answer being written down by a randomly selected child.)

*Logic*: Subjects will be asked to judge the correctness of 25 logic statements. For example: A follows B in “AB” (false), B is not preceded by A in “BA” (true). The number of already-completed correct number is measured for score [34]. (Correct rate (%) = right numbers (n)/already-completed numbers (n) × 100%).

### 2.15. The Possible Potential Harm of the Study on Subjects

Subjects will be fasting without water, which may induce hypohydration. Health effects of insufficient water intake include emergency of the sensation of thirst, decreased physical activity, increased plasma osmotic pressure and reduction of urine. If subjects in the study appear side effects and harmful responses, professional medical staff will give treatment timely. 

Subjects can withdraw from the trial at any time following their own requirements. If subjects in the study appear side effects and harmful responses, they can withdraw the trial freely and be given timely treatment by researchers.

### 2.16. Auditing of Trial Conduction

Trial conduction will be audited by competent authority in the college every day, and the process will be independent from investigators and the sponsor.

### 2.17. Strategies to Improve Adherence to Intervention Protocols

The principles and requirements of the study will be fully explained and anyone who fails needs to let researchers known. In order to improve adherence, the researchers will meet and communicate with subjects every day in order to find problems and handle them timely. The reasons and time for drop-out will also be recorded in detail. The urine biomarkers will be evaluated by Data monitoring committee (DMC) once a day for monitoring adherence. 

### 2.18. Confidentiality

Researchers will keep the information confidential for the subjects. The names of subjects will be coded as study ID during, and after the trial.

### 2.19. Data Collection, Entry and Statistical Analysis

Data collection: Researchers will be trained about the trial process, the use of questionnaires and laboratory tests. Subjects will be trained to be familiar with the related questionnaire and the requirements in the study. Some indicators are measured twice to ensure their accuracy, such as height, weight, waist circumstance and blood pressure. If subject withdraw the trial, his data will not be analyzed. All the questionnaires will be stored for regularly checked and rechecked by data monitoring committee. 

*Data entry*: All data will be recorded and entered into Epi Data 3.1 twice to ensure the accuracy by trained researchers. 

*Statistical analysis*: SAS 9.2 (SAS Institute Inc., Cary, NC, USA) will be used for statistical analyses. Quantitative parameters for subjects will be presented as mean ± standard deviation; binary classification data (hypohydration) will be presented as n ± percentage. Quantitative parameters at test 1 between two groups will be compared with the method of Student’s *t*-test (for normally distribution) and Mann-Whitney *u*-test (for abnormally distribution); binary classification data (hypohydration) at test 1 between two groups will be compared with the method of Chi-square test. Mixed model of repeated measures (ANOVA) will be used to investigate the effect of water supplementation on changes in urine index, mood and cognitive performances, whilst covarying age, BMI, hunger, satiety, sleepiness, blood pressure, blood glucose, body area and fluid intake. Significance levels will be set at 0.05 (*p* < 0.05, 2-tailed) with 95% confidence intervals (95% CI). Data of subjects without compliance will be included in data analysis.

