### 2.3. Sample Size Calculation

The variable used for the calculation of sample size is digit span. Digit span is used to assess short-term memory. It was reported that the average values of digit span for subjects with water supplementation and without water supplementation were 10.5 and 11.5, respectively [18]. The values was taken as reference for our study and 80% power is set. SAS 9.2 (SAS Institute Inc., Cary, NC, USA) is used to calculate the sample size. Only male students will be studied, for the reason that women’s menstrual cycle may have impacts on urine indicators and cognitive performances. In addition, 10% drop-out rate is taken into account. Eventually, a total of 68 subjects will be needed. 

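### Excluding every subject who withdraws, with no limit to withdrawals before allocation, can drop randomised men with collected data and bias the comparison

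*Protocol article*

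**What the plan says.** Two sentences in section 2.19 of the protocol article define who is analysed. Under data collection: "If subject withdraw the trial, his data will not be analyzed". At the end of the statistical analysis paragraph: "Data of subjects without compliance will be included in data analysis". Neither mentions randomisation or the time of the event.

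Withdrawal is open throughout. Section 2.15: "Subjects can withdraw from the trial at any time following their own requirements". Section 2.6.6, which describes the intervention itself: "During the period of the study, subjects can quit at any time for side effects, such as syncope".

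Section 2.6.5 fixes the time of allocation: "On day 9 (the water supplementation day), all subjects will be asked to arrive at the designated place at 8:00 AM". Assignment to 34 and 34 follows, then test 1 cognition and mood at 8:30 AM. By section 2.6.6 the drink is at 9:00 AM, and cognition and mood are repeated from 10:25 AM. Table 2 gives allocation and intervention the same date. Section 2.3 says of the sample size: "10% drop-out rate is taken into account".

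**The concern.** Randomisation protects the comparison only if the men compared are the men randomised. A rule that removes men for something they do after allocation gives up that protection when the reason for leaving is related to both arm and outcome.

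Here that is possible on the protocol's own reasoning. Side effects are a named reason to leave (section 2.6.6). Going without water is said to risk hypohydration (section 2.15). The study hypothesis (section 2.1) is that hypohydration impairs cognition and mood. From 9:00 AM one arm has had 400 mL of water and the other none. If men who feel unwell leave the no-water arm more often and would have scored poorly, excluding them flatters that arm and dilutes a benefit of water. Blinding the analysts to group labels (section 2.7) does not correct selection into the data set.

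A second, smaller matter is that the article does not separate a non-complier, who is kept, from a withdrawal, who is excluded. A man who breaks the procedure and then leaves falls under both sentences.

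**Working it through.** **1. Can a randomised man with data be excluded?** Order of events on day 9 (sections 2.6.5 and 2.6.6): arrival at 8:00 AM and allocation; test 1 cognition and mood at 8:30; the drink, or none, at 9:00; test 2 blood pressure, glucose and urine from 10:05; test 2 cognition and mood from 10:25. A man who leaves at 9:30 has been allocated and has test 1 data, yet is not analysed. Read literally, so is a man who completes test 2 and withdraws before close-out (Table 2). Withdrawals on days 1 to 8 come before allocation, and leaving those out does no harm.

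**2. A scale for the outcome.** Section 2.3 gives a digit span difference of 1.0 (10.5 and 11.5; only the size is used here), 80% power, 10% drop-out and N = 68. It states no SD, so N cannot be reproduced directly. Solving backwards with two-sided 0.05 (the level in section 2.19):

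n per arm = 2 × (1.960 + 0.842)² × SD² / 1.0² = 15.70 × SD²

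- SD 1.38: 15.70 × 1.904 = 29.9, so 30; 30/0.9 = 33.3, so 34; total 68.
- SD 1.35 gives 66 and SD 1.40 gives 70. SD 1.30 gives 60 and SD 1.45 gives 76.

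An SD of about 1.38 is therefore implied, not stated.

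**3. Shift in one arm's mean.** Let a fraction p of the arm leave, scoring a gap g below those who stay. The full-arm mean is (stayers' mean) − p × g, so the analysed mean is too high by p × g. Assume g = one SD = 1.38:

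| Lost from one arm | p | Shift (digits) | Share of 1.0 |
|---|---|---|---|
| 1 of 34 | 0.029 | 0.04 | 4% |
| 2 of 34 | 0.059 | 0.08 | 8% |
| 10% of the arm | 0.100 | 0.14 | 14% |
| 7 of 34 | 0.206 | 0.28 | 28% |

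The last row puts the whole allowance (10% of 68 = 6.8, about 7) into one arm. The shift is proportional to g, so a gap of half an SD halves every figure. It carries over to the between-arm difference only if the other arm has no similar loss.

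**4. Effect on the test.** A simulation with no true effect used 34 per arm, a two-sample t-test and 40,000 runs, with 1, 2, 3 or 4 men removed from one arm.

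- If removal has an assumed correlation of 0.5 with the outcome, the type I error is about 5.3%, 5.9%, 6.6% or 7.4%.
- If the lowest scorers are removed (worst case), it is about 6.3%, 8.6%, 12.3% or 16.1%.

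**5. Numbers analysed.** If the whole 10% left after allocation, 68 × 0.9 = 61.2, so about 61 or 62 men would be analysed instead of 68.

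**The case against.** The strongest reply is that the rule will rarely apply to a randomised man. The 10% allowance is for a nine-day study with seven days of fluid records and three days of food weighing. The window that matters lasts about 2.5 hours, and for the first hour the arms are treated alike. This stands, and it makes the first two rows of the table the realistic ones.

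A reader might infer that only the no-water arm goes on fasting, so that the rule must remove the worst-affected controls. The article does not support this. Section 2.6.6 keeps both arms from food and further drink until test 2, so they differ only by the 400 mL. Both are also asked not to pass urine, which might itself make men in the water arm leave. Nor does the article attribute the side effects to fasting.

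A reader might also set leavers one SD below the whole-arm mean and get p/(1 − p) × 1.38, that is 0.15 and 0.36 digits for the last two rows. That is a larger assumed gap than one SD below those who stay.

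The planned analysis concerns changes. A man who is low at both tests need not bias a change, so raw-score shifts are only a guide.

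Not analysed does not mean destroyed: questionnaires are stored (section 2.19), reasons and times of drop-out are recorded (section 2.17), and the abstract commits to CONSORT reporting. This helps with transparency and makes repair possible, but the men remain outside the analysis.

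Finally, a separate analysis plan might define the analysis set. What is at issue, however, is a rule that the article states, not a detail that it omits.

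**Conclusion.** The point holds in a limited form. The stated rule allows randomised men with collected data to be excluded for something that happens after allocation, and nothing in the article restricts it. It could bias the comparison. Dilution of a water benefit is plausible, but the documents do not establish the direction.

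The expected size is small: about 0.04 to 0.08 digits for one or two losses in one arm. About 0.14 is an upper illustration and about 0.28 an extreme. These figures rest on an assumed one-SD gap, a back-solved SD and informative loss in one arm only.

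Keeping non-compliers is sound and is not part of the fault. A reader might see the two sentences in section 2.19 as a flat contradiction. They are not one, but the boundary between the two groups is undefined and should be reconciled. With 34 men per arm, and a remedy this cheap, the rule should be changed before analysis.

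**What to change.** Replace the withdrawal sentence in section 2.19 with: *All randomised subjects are analysed in their allocated group using all data collected up to withdrawal, unless consent to use of the data is withdrawn.* Withdrawals before allocation may still be left out. Then:

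- Define non-complier and withdrawal so that no man falls under two rules. Under the new sentence the label no longer decides who is analysed.
- Invite men who stop the procedure to complete test 2 if they are willing. This is the only step that recovers the missing outcome.
- State that the planned mixed model is fitted by likelihood, so that incomplete pairs are retained. The article names no estimation method. A man with test 1 only adds little, and this step does not remove bias if leaving depends on unobserved deterioration.
- Report withdrawals by arm with time and reason, and add a sensitivity analysis that assigns leavers poor test 2 scores, in both arms and then in each arm alone.

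The cost is one sentence, two definitions and one extra table. Drop-out reasons and a mixed model are already planned. Table 1 lists recruitment as finished. If day 9 has passed, the test 2 invitation comes too late, but the other changes can still be made from the stored questionnaires.
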